### Sample size and recruitment

The target sample size is *N* = 252 patients from *n* = 14 clusters (126 participants from 7 intervention wards and 126 participants from 7 control wards). Power calculation estimated *N* = 180 participants (*n* = 12 clusters) to be analysed in order to detect an expected Cohen’s d of 0.45–0.5 in the primary outcome of SDM-Q-9 with a power of at least 80% at two-sided alpha of 0.05 assuming ICC = 0.02. These assumptions are based on data from a comparable study (SDM-PLUS), which involved a similar population and the same main outcome parameter [38]. Due to an assumed drop-out rate of patients of 15–25% and to account for a potential drop out of clusters, we aim at recruiting *n* = 14 clusters and *N* = 252 patients.

Patient recruitment will be conducted by a trained study staff and will take place on the 14 selected wards at three hospitals in Munich, Germany (Klinikum rechts der Isar of the Technical University of Munich, kbo-Isar-Amper-Klinikum München-Ost and München-Schwabing). These hospitals with more than 1500 beds in total can facilitate the enrolment of the planned number of patients (*N* = 252) in a timely manner, as in our previous trials [38, 54].

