### Data analysis

The effect-size for continuous outcomes will be the mean difference (MD) and for dichotomous outcomes will be the odds ratio (OR), presented with their 95% confidence intervals. Per-protocol analysis will be conducted, i.e., by excluding patients with no outcome data, patients that do not receive at least one session of SDM-assistant, patients who moved from a ward belonging to the control group to a ward belonging to the intervention group or vice versa. There will be no imputation of missing outcome data, and observed cases will be used.

The primary outcome (SDM-Q-9 at T1) and secondary continuous outcomes will be analysed with mixed-effects linear regression models fitted with ward (cluster) as a random-effects term and with intervention/control group as a fixed-effects term. In a similar vein, dichotomous outcomes will be analysed with logistic regression models using the generalised estimating equations (GEEs).

The robustness of the results of the primary outcome will be investigated in a sensitivity analysis by adjusting for baseline covariates such as severity of illness, admission status and variables with a large baseline imbalance.

In addition, we plan exploratory subgroup analyses in order to investigate if there is potential effect-modification of patient characteristics (e.g., age, sex, symptom severity, duration of illness) on the primary outcome.

Alpha will be set at two-sided alpha of 0.05.

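### Logistic GEE on 14 wards (possibly 12) with no small-sample correction stated: the ordinary robust z test would run at about 8–10% rather than 5% for the secondary binary outcomes, or about 5–8% if the ward matching works

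*Protocol article*

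**What the plan says.** In the protocol article, Data analysis, continuous outcomes get a linear mixed model with ward as random effect, and "dichotomous outcomes will be analysed with logistic regression models using the generalised estimating equations (GEEs". Odds ratios are reported with 95% confidence intervals, and "Alpha will be set at two-sided alpha of 0.05". The section does not name the variance estimator, the working correlation, the reference distribution or any small-sample correction.

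Under Sample size and recruitment, "The target sample size is *N* = 252 patients from *n* = 14 clusters", split as "126 participants from 7 intervention wards and 126 participants from 7 control wards". The power calculation itself uses 180 analysed patients in 12 clusters, "with a power of at least 80% at two-sided alpha of 0.05 assuming ICC = 0.02". The excess covers "an assumed drop-out rate of patients of 15–25% and to account for a potential drop out of clusters".

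Under Randomization and blinding, the wards form seven matched pairs with one ward of each pair randomised to each arm. The models under Data analysis contain no pair term.

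No outcome is explicitly labelled dichotomous. Readmission, which the outpatient psychiatrist documents at three months, is the natural one. The Abstract and Discussion list rehospitalizations as a secondary outcome.

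**The concern.** The GEE sandwich variance is justified by a large number of clusters, not of patients. With seven wards per arm it is biased downwards, and a normal reference ignores the uncertainty in a variance estimated from 14 ward-level residuals. Both errors act in the same direction: standard errors too small, intervals too narrow, and more than 5% false positives under no effect.

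At stake is any claim on a binary outcome. The Background and the Discussion present fewer rehospitalisations as a hoped-for benefit of the tool. An interval labelled 95% that covers nearer 90–92% would overstate the evidence for that claim.

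**Working it through.** **Inputs from the article.** 14 wards, 7 per arm, 252/14 = 18 patients per ward. After 15–25% drop-out, 18 × 0.85 = 15.3 to 18 × 0.75 = 13.5 per ward. The power calculation has 180/12 = 15 per ward. Alpha is 0.05 two-sided. ICC 0.02 is given for SDM-Q-9 only.

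**The plan's own figure.** Design effect 1 + (15 − 1) × 0.02 = 1.28. At d = 0.475, the middle of the stated range, n per arm = 2 × (1.96 + 0.842)² / 0.475² = 69.6, so 70. Then 70 × 1.28 = 89.6, so 90 per arm and 180 in all. The stated number is reproduced. It concerns the continuous primary outcome and gives no assurance about the binary analyses.

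**Analytic check for GEE.** With m equal-sized wards per arm, the uncorrected sandwich variance is too small by about (m − 1)/m. The properly scaled statistic follows roughly a t distribution on 2m − 2 degrees of freedom. The real level of a nominal 5% z test is then P(|t| > 1.96 × √((m − 1)/m)).

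- 14 wards: 1.96 × √(6/7) = 1.815, and P(|t₁₂| > 1.815) = 0.095.
- 12 wards: 1.96 × √(5/6) = 1.789, and P(|t₁₀| > 1.789) = 0.104.

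**Simulation under no effect.** Assumptions, none of them given in the article: beta-binomial wards, event rate 10–50%, ICC 0–0.05, coefficient of variation of ward size 0–0.6. There were 40,000 runs per setting (20,000 with pair correlation), with a Monte Carlo standard error of about 0.15 percentage points. The working correlation was fixed at the true ICC.

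| Setting, uncorrected sandwich, z | Type I error |
|---|---|
| 14 wards, equal sizes | 8.1–9.6% |
| 14 wards, unequal sizes | 9.0–9.9% |
| 12 wards, equal sizes | 9.2–10.4% |
| 12 wards, unequal sizes | up to 11.1% |
| 14 wards, within-pair correlation 0.3, pairs ignored | 8.0% (ICC 0.02), 7.1% (ICC 0.05) |
| 14 wards, within-pair correlation 0.6, pairs ignored | 7.2% (ICC 0.02), 5.4% (ICC 0.05) |

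The paired rows use an event rate of 30%.

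**Check with a standard GEE routine** (exchangeable correlation estimated, 1,500 runs, standard error about 0.7 points): 8.7–9.7% with 14 wards and 9.6% with 12. The model-based variance from the same fits gave 8.0–9.7%, so choosing it instead of the sandwich does not remove the problem.

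**After correction.** Without pair correlation:

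| Method | 14 wards, equal sizes |
|---|---|
| Uncorrected sandwich, t(12) | 5.4–6.6% |
| Kauermann-Carroll, t(12) | 3.8–4.9% |
| Mancl-DeRouen, z | 4.4–5.5% |

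With unequal sizes, Kauermann-Carroll with t(12) gives 4.2–5.2%. Where pairs are correlated and ignored, it becomes conservative: 2.5–4.1% in the four paired settings.

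**Primary outcome.** A balanced linear mixed model tested by Wald z gave 5.5% at the planned ICC of 0.02, 6.6% at 0.05 and 7.2% at 0.10.

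**The case against.** The strongest reply is that the article is silent rather than wrong. It condenses a fuller protocol, and the variance correction and degrees of freedom are often left to the analysis plan, which is not shown. GEE is not itself a faulty choice, since the remedy can keep it. This stands as a limit on wording: a reader might infer that the trial has decided against a correction, and the article does not support that. It does not dispose of the point. The article commits to a named method, a cluster count and a 5% level, and the ordinary form of that method misses that level at that count.

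A reader might also infer that the error doubles for every dichotomous outcome. That goes too far. The wards are matched, and positive within-pair correlation, if ignored, pulls the error of an unpaired test down to about 5.4–8.0%. The article does not say how strongly the matching will correlate binary outcomes. Nor does it say that the side-effect scales will be dichotomised: UKU items run 0–3 and the patient-reported ANTISIDES items 0–10, so false positives on side-effects through GEE cannot be assumed.

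Finally, a reader might extend the concern to the primary analysis. SDM-Q-9 is not analysed by GEE, the article names no Wald z test for the mixed model, and even that test runs at 5.5% at the planned ICC.

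**Conclusion.** The point holds in conditional form. If the GEE is run with the ordinary sandwich variance and a normal reference, the type I error is about 8–10% at 14 wards (1.6 to 2.0 times nominal) and about 9–11% at 12 (1.8 to 2.2 times). With effective matching that the model ignores, it is about 5–8% at 14 wards. The range rests on assumed event rates of 10–50%, binary-outcome ICCs of 0–0.05, ward-size variation up to 0.6 and within-pair correlations of 0, 0.3 or 0.6. The analytic check and the simulations agree.

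The reach is limited to secondary dichotomous outcomes, chiefly readmission. It should be put right before analysis, but it does not threaten the primary comparison.

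**What to change.** Add one sentence to the analysis section, or confirm that the analysis plan already contains it. Either of these would do:

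- **GEE with a bias-corrected sandwich variance:** Kauermann-Carroll with a t reference on wards minus 2 degrees of freedom, or Mancl-DeRouen with a normal reference. The pairing of correction and reference should be stated, because Mancl-DeRouen combined with t(12) was conservative (2.6–3.5% with 14 equal wards).
- **A within-pair permutation test or a ward-level analysis**, which can respect the matching directly. With seven pairs there are 2⁷ = 128 allocations, so the smallest two-sided p-value is 2/128 = 0.016. With six pairs it is 2/64 = 0.031 and the next is 4/64 = 0.063, so the test becomes coarse if a pair is lost.

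The cost is a software option and wider intervals. With equal wards, Kauermann-Carroll with t(12) widens the log-odds interval by (2.179/1.96) × √(7/6) = 1.20, that is about 20% at 14 wards. Mancl-DeRouen with z widens it by 7/6, about 17%. Design, data collection and sample size do not change.

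Naming Satterthwaite or Kenward-Roger degrees of freedom for the linear mixed models is optional and costs nothing further.

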#### Baseline parameters

We will record at baseline (T0) socio-demographics (i.e., age, sex, nationality, language, education, family and occupation status, digital literacy), anamnesis (ICD-10 diagnoses, duration of illness, number of previous hospitalizations, previously prescribed medications), and information about the current admission (legal status, voluntary or involuntary treatment with antipsychotics).

We will also record patient-related factors that could influence the shared-decision making for selecting treatments, i.e. patients’ participation preferences for decision making using the corresponding subscale of the Autonomy Preference Index [33], insight and perceived necessity of treatment using the Birchwood Insight Scale [34] and perception of the current admission using the MacArthur Admission Experience Survey [35].

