#### Primary outcome

The primary outcome will be patients’ perceived involvement in decision-making using the Shared-Decision-Making Questionnaire (SDM-Q-9) [36] at T1. The SDM-Q-9 is a self-report scale consisting of nine items that describe different parts of the SDM process and reflecting the inpatient decision-making, e.g., here on the selection of antipsychotic medication. Each item will be scored from 0 “completely disagree” to 5 “completely agree”, and a total score will be calculated ranging from 0 to 45, with a higher score indicated a better-perceived involvement [36]. We expect that the use of the SDM-assistant would substantially improve patients’ perceived involvement, thus identifying a clinically meaningful mean difference of at least 15 points in SDM-Q-9 between the intervention and control group [37, 38].

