Side-effects will be recorded using items of the clinician version of the Udvalg for kliniske undersøgelser scale (UKU-SERS) [47] at T0, T1 and T2. The UKU scale consists of 48 items covering a comprehensive list of side-effects grouped in four categories, i.e., psychic, neurologic, autonomic and other side-effects. We will also evaluate two additional items about suicidality and oedema. Each item is scored from 0 to 3 based on the severity with a higher score indicating more severity [47]. It will be administered via a semi-structured interview by the study personnel. The weight of patients will be measured at T0 and T1, and we will ask the patients to report their weight at T2. Furthermore, we developed the patient-reported antipsychotic and antidepressant side-effect scale (ANTISIDES) that will be administered at T0, T1 and T2. The scale consists of 41 items covering a broad spectrum of side effects that can be caused by psychotropic drugs. Each item will be rated on a visual analogue scale from 0 “not at all” to 10 “extremely strong”, supplemented by an assessment of the impairment experienced due to the respective side effect (eAppendix 3).

We will address global functioning using the clinician-rated Social and Occupational Functioning Assessment Scale (SOFAS) [48] at T0, T1 and T2, and quality of life using the patient-reported EUROHIS-QOL [49] at T2.

Treatment satisfaction, attitudes and adherence will be measured using the patient-reported scales Questionnaire on Patients’ Treatment Satisfaction (ZUF8) [39], Medication Satisfaction Questionnaire (MSQ) [50], Drug Attitude Inventory (DAI) [51] and Medication Adherence Rating Scale (MARS) [52] at T0, T1 and T2. Physicians will also rate adherence to the medication treatment at T1 and T2 using a single question scored on a 4-point Likert scale from 1 “very good” to 4 “poor”.

Last, data about the use of the SDM-assistant (e.g., number of sessions, duration of use) will be recorded within the SDM-assistant and evaluated at T1. This information would also be helpful in assessing treatment integrity.

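### Collected baseline values are left out of the main models, and the only adjusted analysis, of the primary outcome, chooses part of its covariates by observed imbalance

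*Protocol article*

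**What the plan says.** **Main model.** The Data analysis section of the protocol article analyses the primary outcome and the continuous secondary outcomes with "mixed-effects linear regression models fitted with ward (cluster) as a random-effects term and with intervention/control group as a fixed-effects term". Dichotomous outcomes get the analogous logistic model through GEE. No baseline value or other covariate is named for either.

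**Where covariates enter.** "The robustness of the results of the primary outcome will be investigated in a sensitivity analysis", carried out by "adjusting for baseline covariates such as severity of illness, admission status and variables with a large baseline imbalance". No adjusted analysis is described for any secondary outcome.

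**What is collected at T0.** The section on secondary outcomes and other variables places PANSS-6 and measured weight at T0 and T1, with patient-reported weight at T2. It places UKU, ANTISIDES, ZUF8, MSQ, DAI and MARS at T0, T1 and T2, and likewise the "Social and Occupational Functioning Assessment Scale (SOFAS) [48] at T0, T1 and T2". Baseline parameters adds legal status, voluntary or involuntary treatment, and "patient-related factors that could influence the shared-decision making for selecting treatments": participation preference (Autonomy Preference Index), insight and perception of the admission. The Outcomes section puts T0 before any use of the tool, so these are usable as baseline covariates.

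**Primary outcome.** It is perceived involvement in "decision-making using the Shared-Decision-Making Questionnaire (SDM-Q-9) [36] at T1". The text names no T0 SDM-Q-9; Table 1 is not shown.

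**The concern.** Two separate choices are at issue.

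First, the main models leave out information that the trial already pays to collect. For an outcome measured at T0, its own baseline is usually the strongest single predictor available. Leaving it out widens the confidence interval and lets any baseline difference between arms pass into the estimate. The Background names side-effects and adherence among the trial's aims, and both are measured at T0.

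Second, part of the adjusted analysis is settled after the data are seen. An imbalance rule with no threshold lets the analyst decide what counts as large. It also selects on the wrong property: a variable that is imbalanced but unrelated to the outcome needs no adjustment, while a strongly prognostic variable repays adjustment even when balanced.

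With only 14 randomised units, noticeable chance differences in patient mix are to be expected.

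**Working it through.** **Inputs from the documents** (Sample size and recruitment): N = 180 analysed in 12 wards, so 180/12 = 15 per ward and 90 per arm; ICC 0.02; d = 0.45–0.5; power at least 80%; two-sided alpha 0.05; 14 wards planned, 7 per arm.

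**Assumed, because the documents give no figure:** the share R² of SDM-Q-9 variance explained by covariates (0.05–0.20), with the ICC held at 0.02 after adjustment; the correlation r of a secondary outcome with its T0 value; the ICC ρ of a baseline covariate.

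**1. The plan's own figure.** Design effect = 1 + (15 − 1) × 0.02 = 1.28. Patients per arm before clustering = 2 × (1.96 + 0.84)²/d², rounded up, then × 2 × 1.28:

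- d = 0.45: 78 per arm, N = 199.7
- d = 0.475: 70 per arm, N = 179.2
- d = 0.50: 63 per arm, N = 161.3

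So 180 reproduces near the middle of the stated range of d.

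**2. Power of the unadjusted model at N = 180.** In SD units, SE = √(2 × 1.28/90) = 0.169. Power = Φ(d/SE − 1.96): about 76% at d = 0.45 and 84% at d = 0.5. Precision is thin at the lower end of the stated range.

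**3. Power with covariates in the primary model.** The SE is multiplied by √(1 − R²).

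| Assumed R² | SE factor | Power, d = 0.45 | Power, d = 0.5 | N needed, d = 0.45 |
|---|---|---|---|---|
| 0 | 1.000 | 76% | 84% | 200 |
| 0.05 | 0.975 | 78% | 86% | 190 |
| 0.10 | 0.949 | 80% | 88% | 180 |
| 0.20 | 0.894 | 85% | 91% | 162 |

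With a t reference on 10 degrees of freedom (12 wards − 2) all powers are lower, but the gain has a similar size: at d = 0.45, 67% unadjusted and 77% at R² = 0.20.

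**4. Secondary outcomes with their own T0 value.** Adjustment multiplies patient-level variance by 1 − r²: 0.84 at r = 0.4, 0.75 at r = 0.5, 0.51 at r = 0.7. A change-score analysis with equal variances multiplies it by 2(1 − r): 1.2, 1.0 and 0.6. At each of these correlations adjustment is the more precise of the two.

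**5. Chance imbalance with 7 against 7 wards of 15.** The SD of the standardised baseline difference is √(2 × (1 + 14ρ)/(7 × 15)).

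| Assumed ρ | SD of difference | Chance that it exceeds 0.2 SD |
|---|---|---|
| 0.02 | 0.16 | 20% |
| 0.10 | 0.21 | 35% |
| 0.20 | 0.27 | 46% |

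Any gain from matching wards is ignored here. With an assumed covariate–outcome correlation of 0.3, a typical (one-SD) imbalance shifts the unadjusted estimate by about 0.3 × 0.16 = 0.05 to 0.3 × 0.27 = 0.08 outcome SDs, against a target of 0.45–0.5.

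**The case against.** **Silence in a condensed article.** The article does not say that group is the only term. It also leaves open whether secondary outcomes are analysed as raw T1/T2 values or as change from T0; for symptoms it speaks of improvement as well as severity. Terms for individual scales might be set elsewhere. Part of this stands: the form of the secondary response is not stated. The objection still fails, because the article does list the model terms and places adjustment explicitly in a sensitivity analysis of one outcome. That is a stated choice, and a change score would not match the precision of adjustment (step 4).

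**The sensitivity analysis is better than it may look.** A reader might infer that its covariates are chosen wholly by imbalance, or that imbalance in the primary outcome is never corrected. The text supports neither. Severity and admission status are named in advance, and the primary outcome does get an adjusted result.

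**Randomisation and matching.** Randomisation itself does not bias the unadjusted estimate, and seven pairs of comparable wards should limit ward-level differences. Both points stand. They reduce the concern about imbalance but do not restore the lost precision.

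**No internal contradiction.** A reader might infer that recording factors thought to influence shared decision-making, then leaving them out of the model, contradicts the plan. It does not: the plan also means to explore factors that affect use and effects of the tool, and includes exploratory subgroup analyses.

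**Size.** A reader might carry correlations of 0.4–0.7 over to SDM-Q-9, or expect a dramatic narrowing for body weight. The documents support neither. The text names no T0 SDM-Q-9, and it gives no SD or baseline correlation for weight. For the primary outcome the gain may be small: 2 percentage points of power at R² = 0.05.

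**Conclusion.** The point holds as a weakness of analysis choice that costs almost nothing to correct. The stated main models use none of the baseline values collected for PANSS-6, UKU, ANTISIDES, weight, SOFAS, ZUF8, MSQ, DAI and MARS. The one adjusted analysis combines two pre-named covariates with an open, data-driven rule.

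For the primary outcome the gain is modest and rests on an assumed R²: at 5–20%, a standard error about 2.5–11% smaller and power of 78–85% instead of about 76% at d = 0.45 and N = 180. For secondary outcomes the gain is larger if their baseline correlation is higher, but the documents do not allow it to be quantified.

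It should not be inferred that adjustment would repair selective recruitment on unblinded wards or the per-protocol exclusions. It can reduce measured imbalance; it does not restore the randomised comparison.

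**What to change.** 1. In the model for every outcome measured at T0, add that outcome's T0 value as a fixed effect.
2. In the primary SDM-Q-9 model, add a short list fixed in advance from variables already collected, for example baseline severity (PANSS-6 at T0), legal or admission status, and the participation-preference subscale of the Autonomy Preference Index. Define each one, including how it is coded.
3. Report the present unadjusted model as the sensitivity analysis.
4. Delete the rule that adds variables with a large baseline imbalance.

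**Cost.** Analysis wording, a few patient-level degrees of freedom, and a simple stated way of handling missing baseline values. No new data are needed. With 12 to 14 wards, ward-level terms should stay few; the covariates listed here are patient-level.

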## Discussion

Choosing an antipsychotic medication is an important medical decision that should require benefit-risk assessments and the active involvement of patients whenever possible (i.e., shared-decision making) [4, 5]. In order to facilitate shared-decision making for choosing antipsychotics, we developed an evidence-based shared-decision making assistant (SDM-assistant). In the planned cluster-randomised trial, we will examine the use of SDM-assistant for choosing antipsychotics in hospitalized patients with an acute exacerbation of schizophrenia. We will evaluate the perceived involvement of patients in the decision-making as primary outcome, and therapeutic alliance, symptom severity, side-effects, treatment satisfaction, adherence, quality of life, functioning and rehospitalizations as secondary outcomes.

There are potential methodological limitations and challenges.

First, the SDM-assistant aims to present high-quality evidence from a network meta-analysis on the efficacy and side-effects of antipsychotics [1]. However, not every important side-effect is covered, for example cognitive and sexual side-effects (yet prolactin elevation used as a proxy of sexual side-effects, as discussed above) [56, 57], since they have not been well examined in network meta-analyses. In addition, the current version of SDM-assistant is focusing on the selection of antipsychotics in the acute phase, and other aspects of antipsychotic treatment are not considered, long-term treatment, management of adverse events, switching antipsychotics, dosing etc. Moreover, we focused on medication issues, yet we acknowledge that the treatment of schizophrenia is multimodal, e.g., psychological treatments have also a major role [58, 59]. In future updates, SDM-assistant could implement new data from network meta-analysis (or other sources of high-quality evidence), expand the list of side-effects and antipsychotics, as well as consider additional treatment modalities (e.g., psychological treatments and non-invasive brain stimulation) and extend the framework to facilitate a broader range of decisions. Additional features could also be added such as giving the option to select different effect-size indices (e.g., absolute percentages) [29] or different plots for presentation (e.g., Cates or Kilim plots, etc.) [60, 61]. Furthermore, recent meta-analytic methods that have been developed to individualise treatment recommendations, e.g., [62, 63] were not yet implemented. The use of such complicated methods in shared-decision making requires caution, since they could swift decision-making to a computerised paternalistic process that is heavily dependent on statistical assumptions [16].

Third, there are certain difficulties in the implementation of the intervention. Shared-decision making can be successful, yet challenging, in acutely ill inpatients with schizophrenia, potentially due to reduced decisional capacity, high severity psychotic symptoms, cognitive impairment, lack of insight, and negative attitudes towards the treatment [64–66]. The use of the SDM-assistant could make the process even more demanding due to the higher attention and cooperation requirements. For these reasons, we will use a mixed-methods approach to evaluate barriers and facilitators for the implementation of the intervention. SDM-assistant aims to enable patients to get familiar with the evidence and participate in the decision-making, without forcing them to be involved. In those cases, a more paternalistic decision-making approach with the physician choosing a suitable medication might be still acceptable [18]. Nevertheless, the early involvement of patients in the selection of antipsychotics can be very important in order to prevent burdensome side-effects, since at least some of them could be subjectively realized only later after the improvement of symptoms, e.g. rapid weight gain [67]. Third, treatment-as-usual will be used in the control group, instead of an active control group (e.g., using paper forms to present evidence on antipsychotics or unspecific group training) in order to avoid contamination. However, it is possible that the increased attention in the intervention group could inflate any differences found.

In conclusion, we developed SDM-assistant, an SDM assistant that presents high-quality evidence on the efficacy and side-effect profile of antipsychotics and can be used as a framework for shared-decision making between physicians and patients with schizophrenia when selecting antipsychotic medications. The major aim of the planned trial is to show that the use of SDM-assistant leads to increased patients’ perceived involvement in the decision-making process as well as to a more suitable selection of antipsychotics, as reflected by our secondary outcomes (e.g., symptom severity, side-effects, adherence, treatment satisfaction, rehospitalizations). The implementation of this intervention is challenging in acutely ill patients with schizophrenia, and potential barrier and facilitators will be examined. Last, according to one of the principles of evidence-based medicine [68], we hope that SDM-assistant can successfully advance evidence-based medicine in schizophrenia by putting medical evidence on antipsychotics into the context of patient preferences and values.

